### 4. Indicate the characteristics of study population:

(a) Gender: Males yes X no \_\_\_\_\_  
Females yes X no \_\_\_\_\_  
(b) Age range: from 50 to 80  
(c) Racial and Ethnic Groups:  
Caucasian yes X no \_\_\_\_\_  
Black yes X no \_\_\_\_\_  
Hispanic yes X no \_\_\_\_\_  
American Indian yes \_\_\_\_\_ no X  
Alaskan Native yes \_\_\_\_\_ no X  
Asian/Pacific Islander yes X no \_\_\_\_\_  
Other (specify) \_\_\_\_\_

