13. Indicate how potential subjects will be identified and recruited for participation in the study:

A flyer/email will be sent in a targeted email to all employees fifty years of age and older. EMC will send the flyer/email, not ISA. The flyer/email will indicate that the study is focusing on employees 50 years of age and older. Interested employees who fit the inclusion criteria (age 50 and older) will be asked to contact ISA at the study e-mail or telephone number. Even

though the flyer will be sent specifically to employees 50 years of age and older, the Project Manager will confirm the age at that time employees contact ISA.

When an employee contacts ISA, they will be provided with additional information about the project (see attached summary of what employees will be told when they contact ISA). The Project Manager will address any questions employees have and will then ask two questions to ensure that the employee qualifies for the study (age and whether they are an EMC employee).

14. Indicate when and where consent will be obtained:

Consent will be obtained as part of the first survey data collection. It will be imbedded into the online survey and participants will not be able to continue with the survey until they have acknowledged and indicated that they consent.

15. Indicate how you will determine whether the subjects (or their surrogates) understand the information that was provided in the consent document:

Participants will be asked to indicate on the consent document that they understood the information on the consent form. The telephone number for the project manager and IRB chair will be included if the participant has questions. A hard copy of the consent document will be e-mailed to participants.

16. Summarize, in a narrative what actually will be done to the subjects during their participation in the study. Make certain that the following are included:

- (a) a clear description of what is being done for research purposes and what is being done as part of standard clinical care;
- (b) a list of tests and procedures that will be performed for research purposes (e.g. blood tests, urine tests, cultures, interviews, questionnaires, surgical procedures, cardiac catheterization, pulmonary function tests, X-rays, scans, etc);
- (c) a brief description of the analyses that will be performed on the biologic or non-biologic (i.e. questionnaires) samples collected;

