## **Outcome Measures**

A draft copy of the survey questionnaire is attached. Most of the measures will be self-report scales of health behaviors that the ISA research team has used in several research projects during the past decade (e.g., Cook et al., 1996a, 1996b, 2004, 2005, 2007; Deitz et al., 2005; Billings et al., 2008)) and will therefore have the typically desired psychometric underpinnings -- established reliability coefficients, validity estimates, etc. -- as described below. In addition, several of the scales were developed and validated by other investigators -- e.g., Block et al., 1986; Schwarzer and Renner, 2000; Glynn and Ruderman, 1986 -- but have demonstrated evidence of reliability and validity. For all scales, however, psychometric analyses will be conducted on the measures once the data are in order to ensure that the collection of items can be legitimately summated; e.g., whether they have high Alpha coefficients and high item-total score correlations. The questionnaire will include the following measures:

☐ **Demographics** -- Items assessing respondents' age, ethnicity, marital status, education, and income. These items have been associated with differences in health outcomes and will be

used as control variables in our multivariate models. They may also be used in interaction terms, or as moderators when applicable.

- ❑ **Symptoms of Distress** – A 15-item scale developed by Orioli et al. (1991) and used in multiple studies by our team (Cook, et al., 2003; Billings et al., 2008). Four items assessing the behavioral signs of stress (e.g., overeating, criticizing others) were summed with four other items assessing the physical signs of stress (e.g., muscle tension, headache). A recent randomized trial (Billings et al., 2008) generated an Alpha of .069. Evidence of validity was generated from Cook et al. (2003) and Billings et al. (2008) where the measure showed significant decreases in subjects exposed to stress management interventions.

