Confounding. Though randomization of 150 participants to each condition makes it unlikely that there will be any imbalance of prognostic factors between the two conditions, confounding remains a possibility in any single realization of an experiment. Left alone, such imbalance could confound the true relationship between condition and the outcomes. In order to avoid this problem, we will examine prognostic factors measured at baseline for evidence of any imbalance; if it is present, we will perform secondary analyses in which we repeat the primary analysis adding the potential confounders as additional covariates in the ANCOVA, attending carefully to issues of measurement error, which can create problems for such adjustments. Regression adjustment cannot completely correct for confounding, but to the extent that the confounders are well measured and properly modeled, the adjusted analysis will reduce the bias created by those confounders.

Effect modification. Other secondary analyses will explore the assumption of homogeneity of the intervention effect across subgroups of participants. Though power will be limited for interactions, we will add a subgroup main effect and a condition x subgroup interaction to the ANCOVA in order to explore possible interactions. The primary subgroup variables will be gender, age group, and racial or ethnic group.

Alternative analytic strategies. Several alternative analytic strategies were considered. The data could be analyzed using a repeated measures analysis of variance model, wherein condition, time (baseline and the two posttests) and their interaction are included as independent variables. However, this approach tends to have less power than the analysis proposed here, and it also makes unnecessary assumptions about the structural relationship between the baseline and posttest values of the outcome variables. For those reasons, we prefer the ANCOVA.

(D) a list of investigational devices that will be used, indicate if they are classified as significant risk (SR) or non-significant risk (NSR) devices and whether there is an IDE or there is an application to the FDA for an IDE if the device is SR;

N/A

(E) a statement that defines who will be financially responsible for the costs associated with participation in the study (e.g. examinations, procedures, drugs, devices, etc.) and a statement that defines what will be provided without cost to the subjects;

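### The age interaction is specified on age group although age is collected from every participant; if the effect changes steadily with age, grouping costs power in a test the plan already calls limited

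*Protocol*

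**What the plan says.** Protocol item 16(C), Effect modification, sets the purpose: "Other secondary analyses will explore the assumption of homogeneity of the intervention effect across subgroups of participants". The method is also given: "we will add a subgroup main effect and a condition x subgroup interaction to the ANCOVA in order to explore possible interactions". The variables are then named: "The primary subgroup variables will be gender, age group, and racial or ethnic group". On power the paragraph says only "Though power will be limited for interactions". It gives no figure, no number of age groups, no cut-points and no reason for grouping.

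Elsewhere in the protocol:

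- **Age is collected.** Outcome Measures (16(B), Demographics) lists items on "age, ethnicity, marital status, education, and income". Item 13 says that "the Project Manager will confirm the age at that time employees contact ISA".
- **Other use of the demographic items.** The Demographics entry adds: "They may also be used in interaction terms, or as moderators when applicable". It does not say how age would be coded there.
- **Age distribution.** Item 4 gives "Age range: from 50 to 80". No mean, SD or shape is stated.

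**The concern.** Gender and racial or ethnic group are categorical by nature. Age is not, and the protocol chooses to turn it into groups before testing whether it modifies the effect. When a modifier acts gradually, grouping treats people of different ages within a group as identical and discards the within-group spread, which carries information on the trend.

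That matters more where power is already short, as the plan says it is here. Age is one of only three named subgroup variables in a trial of a programme built for workers aged 50 and over, so whether the effect holds up with increasing age is a natural question. A weak test is easily misread as evidence that the effect is the same at all ages.

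**Working it through.** **Is there a stated figure to reproduce?** No. The protocol gives no power, effect size or SD for any interaction.

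**Is limited power a fair description?** Yes. With 1:1 allocation and an even two-way subgroup split, the standard error of the interaction is twice that of the main effect. If the main effect has 80% power (two-sided 5%, standardised effect 1.96 + 0.84 = 2.80), an interaction of the same size has 2.80/2 = 1.40. Its power is P(Z > 1.96 - 1.40) = P(Z > 0.56) = 29%.

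**Inputs**

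- From the protocol: 150 + 150 randomised; loss of up to 20%, so 300 x 0.80 = 240 observed; two-sided 5% (stated for the intervention effect, assumed here for the interaction); ages 50 to 80.
- Assumed: the effect changes linearly with age; several age shapes; and, as a benchmark only, 80% power for the interaction on age in years.

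**Formulae**

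- Information kept, k = between-group variance of age / total variance of age.
- Two groups (1 df): power = P(Z > 1.96 - 2.80 x sqrt(k)).
- g groups tested jointly: noncentral F with g - 1 df, and noncentrality k times that of the continuous test.

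**Two groups, split at the median**

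| Assumed age shape | k | Power (80% with age in years) |
|---|---|---|
| Uniform 50-80 | 0.75 | 68% |
| Normal, mean 57, SD 5, truncated to 50-80 | 0.66 | 62% |
| Half-normal from 50 (scale 7), truncated at 80 | 0.62 | 59-60% |
| Exponential from 50 (mean 7), truncated at 80 | 0.55 | 55% |
| Exponential from 50 (mean 5), truncated at 80 | 0.51 | 51% |
| Exponential from 50, untruncated | 0.48 | 49% |

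Worked example, uniform: sqrt(0.75) = 0.866; 1.96 - 2.80 x 0.866 = -0.465; power 68%. For the untruncated exponential, k = (ln 2)^2 = 0.48; 1.96 - 2.80 x 0.693 = 0.02; power 49%. In effective sample size this is 240 x 0.48 = 115 to 240 x 0.75 = 180.

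**More than two groups, joint test (shapes within 50-80)**

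| Grouping | Information kept | Power |
|---|---|---|
| Tertiles | 68-89% | 53-65% |
| Quartiles | 77-94% | 52-61% |
| Five-year bands | 89-97% | 49-53% |

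Finer bands keep more information, but the joint test spends more degrees of freedom, so power stays at about 50-65%. A 1-df trend score across the bands would largely avoid this: with five-year bands and k of 0.89-0.97, the 1-df formula gives about 75-79%. The protocol does not propose one.

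**Sensitivity**

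- Using 300 instead of 240 changes these powers by no more than about 0.002, because the benchmark is fixed at 80%.
- If the benchmark is 50% instead, median splits within the 50-80 shapes leave 29-40%.

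**The case against.** Several points on the other side are sound.

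- **No fixed loss follows from the text.** A reader might infer that the plan as written throws away a quarter to a half of the information. The protocol fixes neither the number of groups nor the cuts. That range belongs to a two-group median split under a linear trend. Five-year bands lose only 3-11% of the information, although a joint test on them is no more powerful.
- **Uneven cuts prove little.** A cut at 65 could look ruinous: it keeps about 13% of the information if age is normal with mean 57 and SD 4. With age uniform over the stated 50 to 80, 65 is the median and the cut keeps 75%. The documents do not supply the input that decides between these.
- **Open cut-points are not a fault here.** Such detail commonly sits in a statistical analysis plan, which is not shown. The point rests on the protocol's choice of a grouped term, not on missing cuts.
- **Age in years is not ruled out.** The Demographics entry allows demographic items as moderators without fixing their coding. It does not, however, change the variable named for the planned test.
- **Age in years is likely but unproven.** The questionnaire is not shown and may ask for bands. The check at first contact is for eligibility.
- **Linearity has a price.** If the effect changes in a step, grouping need not lose power, and a straight line can miss a non-monotone pattern. Groups also answer directly the stated question about subgroups.

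What survives: for a gradual change with age, every joint-tested grouping examined is weaker than age in years, and the protocol gives no reason for grouping.

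**Conclusion.** The point holds as an inexpensive improvement of minor weight. If the effect changes linearly with age, a median split keeps roughly 50-75% of the information, and an interaction that would have 80% power on age in years would have about 49-68%. Three or more bands tested jointly leave about 50-65%.

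These figures depend on assumed age shapes and on a hypothetical 80% benchmark. The true power of this interaction is unknown and, by the plan's own account, limited.

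The analysis is secondary and exploratory. A reader might infer that the trial's main conclusion is weakened, but the documents do not support that: the primary ANCOVA comparison does not use age group, and the number randomised is unaffected.

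**What to change.** In Effect modification, replace the age-group term by age in years: a continuous main effect plus condition by age, fitted in the same ANCOVA. Report the adjusted intervention difference, with its confidence interval, at two or three ages stated in advance. Keep age bands for descriptive display. Use that display, or a pre-specified smooth term, to look for a step or non-monotone pattern.

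First confirm that the questionnaire records age in years. If it offers bands only, a 1-df trend score across the bands is the nearest substitute.

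The cost is a wording change and the small modelling assumption of linearity. It needs no extra participants and, if age is recorded in years, no new data.
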